#### Safety and adverse event monitoring

Interview data are used to document patients’ use of health care during the study period. Medical record review is conducted for details of hospitalizations for AE reporting. At each testing visit at baseline, 12 and 24 weeks, we ask specifically about medical symptoms in the past 12 weeks such as muscle strain, fainting/loss of consciousness, dizziness, worsening shortness of breath or COPD exacerbation, worsening fatigue, falls, palpitations, psychological stress, or other AEs. For any symptom ascertained, we further document the patient’s perception of relatedness to the intervention or testing, severity, any required change in medications, and any further medical care, hospitalization or ER visit. For hospitalizations and ER visits, we further ascertain discharge diagnosis and results of major cardiopulmonary tests or procedures performed. During the intervention, occurrences of adverse events are also queried by instructors and captured in the attendance log, which subjects complete during each class. If a potential AE is reported, study staff contact the participant for further details to determine if a reportable AE has occurred and if so, document the type, whether expected or not, relatedness to the study, and severity. Serious AEs are defined according to our institutional review board’s policy to be an event that is life-threatening, requires hospitalization, results in persistent or significant disability/incapacity or death. Incidents are reported to the IRB, our sponsor, and our Data Safety and Monitoring Board (DSMB) as appropriate.

### Statistical analysis

#### Sample size and power

This study is powered on our pre-specified primary outcomes of overall CRQ (chronic respiratory questionnaire) score and 6-minute walk-test distance. Our effect estimates and standard deviations are based on pilot data of 12-weeks of tai chi versus usual care in patients with COPD [52]. Enrollment of 125 participants will provide approximately 93% power to detect differences between groups of approximately 50 meters change in the 6-minute walk test and 0.9 point change in total CRQ score (mean response value). Our primary comparison will be between the tai chi and education groups, from baseline to 12 weeks in phase 1. It is widely accepted that a change in the 6-minute walk test of 54 meters is clinically significant [81, 101–104]. For the CRQ, Redelmeir *et al*. reported that a 0.5 point change is clinically meaningful [104]. Our study has over 96% power to detect a difference of 54 meters and 99% power to detect a difference of 68 meters (the difference observed in our pilot). These calculations allow for a 5% loss of statistical efficiency of the nonparametric test compared to a *t*-test (for the 6-minute walk), 10% dropout rate, and a conservative Bonferroni correction for multiple outcomes.

For our exploratory dosage aim, we expect to have about 82% power to detect differences between groups of a 50-meter change in 6-minute walk and 0.9 point change in total CRQ. This sample size of 21 per group (12 weeks versus 24 weeks of tai chi) accounts for a 5% loss of statistical efficiency. We expect to have limited power for our second exploratory aim comparing tai chi to the MBB group.

Prior to analyzing the outcomes, we will examine baseline demographic, functional, and clinical variables as well as known prognostic factors (such as baseline GOLD stage and baseline peak VO_2_) by randomized group. Our primary analyses will examine changes between baseline and 12 weeks.

#### Primary aims

##### Efficacy

Changes in total scores on the CRQ will be analyzed using analysis of covariance (ANCOVA), comparing the change from baseline to 12 weeks among the two treatment groups tai chi versus education, adjusted for the baseline value of the outcome (and, if necessary, baseline characteristics found poorly balanced between groups). For the 6-minute walk, the change from baseline to 12 weeks is known to be skewed, so we will use a nonparametric approach and use a Wilcoxon rank sum test to compare the two treatment groups at α = 0.05 (without the Bonferroni correction, given the pilot feasibility nature of the study). As complements to these main approaches, we may use bootstrap analysis to evaluate confidence intervals and the cumulative distribution function with evaluation of the area under the curve for each study arm to show the distribution of patients who improve.

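### The 6-minute-walk primary test is a valid rank test without baseline adjustment; a baseline-adjusted rank test would be slightly more precise at no cost and would match the CRQ analysis

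*Protocol article*

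**What the plan says.** The Efficacy paragraph of the protocol article treats the two primary outcomes differently. Change in total CRQ goes into an ANCOVA "adjusted for the baseline value of the outcome (and, if necessary, baseline characteristics found poorly balanced between groups"). For the walk, because "the change from baseline to 12 weeks is known to be skewed", the plan says "we will use a nonparametric approach and use a Wilcoxon rank sum test to compare the two treatment groups". The significance level for this test is 0.05 with no Bonferroni correction, which the plan puts down to its being a pilot. No covariate is named for the walk. Bootstrap confidence intervals and cumulative distribution functions are possible complements only, and neither is described as adjusted.

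Sample size and power says that baseline variables will be examined by randomised group before the outcomes are analysed. On the choice of test it says: "These calculations allow for a 5% loss of statistical efficiency of the nonparametric test compared to a" *t*-test. It also allows for a "10% dropout rate, and a conservative Bonferroni correction for multiple outcomes". Secondary aims and Exploratory aims 1 and 2 reuse the same approach.

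**The concern.** Skewness is a reason to use ranks. It is not a reason to leave out the baseline, because a rank test can be adjusted for it. Change scores regress towards the mean: patients who start with a low walk distance tend to gain more whatever their arm. A chance difference in baseline walk between 63 and 31 patients therefore passes in part into the comparison of changes. The plan will look at baseline balance by arm, but its walk test has no means of acting on what it finds, whereas the CRQ analysis has.

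At stake are some precision on a primary outcome and how the result reads if baseline walk happens to be unbalanced. The same applies to the smaller comparisons that reuse the test: 21 per group for dosage and 31 in the mind-body breathing arm. The plan also argues in metres (50, 54, 68), while its only definite walk result is a test.

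**Working it through.** **Inputs from the document.** 63 v 31 patients; 10% dropout; 5% efficiency loss; Bonferroni correction in the power calculation (taken as two-sided 0.025 for two outcomes); α = 0.05 in the analysis (two-sided assumed); stated power 93% at 50 m, over 96% at 54 m, 99% at 68 m.

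**Assumed.** ρ from 0.5 to 0.95; equal SDs at baseline and 12 weeks. The document does not print the SD of change, so it is back-solved.

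**1. The plan's own power figures.**
- Effective sizes: 63 × 0.90 × 0.95 = 53.9 and 31 × 0.90 × 0.95 = 26.5.
- √(1/53.9 + 1/26.5) = 0.237.
- SD = 50 / [0.237 × (2.241 + 1.476)] ≈ 56.7 m (55.8 m with a noncentral t).
- Standard error with the efficiency loss: 56.7 × 0.237 = 13.45 m.
- 54 m: 54/13.45 − 2.241 = 1.77, power 96.2%.
- 68 m: 68/13.45 − 2.241 = 2.81, power 99.75%.

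The three stated powers agree with each other. The design effect is 50/56.7 ≈ 0.88 SD of change.

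**2. Gain from adjustment.** With common variance σ², the change has variance 2σ²(1 − ρ) and the baseline-adjusted residual has σ²(1 − ρ²). Their ratio is (1 + ρ)/2. Power = Φ(δ / [13.45 √((1 + ρ)/2)] − 1.960). Without adjustment this gives 96.1% at 50 m and 60.7% at 30 m (α = 0.05).

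**3. Carry-over of imbalance.** The slope of change on baseline is −(1 − ρ), so a baseline difference D shifts the change difference by (1 − ρ)D in size. The baseline SD is 56.7/√(2(1 − ρ)). With 57 v 28 completers the standard error of the change difference is 56.7 × √(1/57 + 1/28) = 13.1 m. A one-standard-error baseline imbalance therefore carries over 13.1 × √((1 − ρ)/2) m.

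| ρ | Variance ratio | Adjusted power, 50 m | Adjusted power, 30 m | Carry-over of 1 SE |
|---|---|---|---|---|
| 0.5 | 0.75 | 99.0% | 73.1% | 6.5 m |
| 0.6 | 0.80 | 98.6% | 70.3% | 5.9 m |
| 0.7 | 0.85 | 98.1% | 67.7% | 5.1 m |
| 0.8 | 0.90 | 97.5% | 65.2% | 4.1 m |
| 0.9 | 0.95 | 96.8% | 62.9% | 2.9 m |
| 0.95 | 0.975 | 96.4% | 61.7% | 2.1 m |

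For ρ 0.6 to 0.95 the gain is 2.5 down to 0.3 points at 50 m and 9.6 down to 1.0 points at 30 m.

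**4. Simulation of the rank tests** (57 v 28, α = 0.05). The comparison is Wilcoxon on change against Quade with the change and the baseline ranked.
- Effect 0.88 SD, gamma-skewed errors: 96.4 v 98.4% (ρ 0.6), 96.8 v 98.2% (0.7), 96.8 v 97.8% (0.8), 97.1 v 97.4% (0.9), 97.1 v 97.2% (0.95).
- Effect 35/57 SD, ρ 0.6/0.7/0.8/0.9:
  - normal errors: 73/73/73/72 v 82/78/77/75%
  - gamma errors: 75/78/77/79 v 84/84/82/81%
  - lognormal errors: 90/93/94/96 v 97/97/97/97%
- Type I error in the second set was 4.2 to 5.6%.

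Two other options do worse. Ranking the 12-week value instead of the change loses power at high ρ (81 v 96% for Wilcoxon, lognormal errors, ρ 0.9). In a separate simulation with lognormal-skewed errors, ordinary ANCOVA lost to the Wilcoxon test on change (77 v 90% at 35 m, ρ 0.9).

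**5. Conditional on imbalance.** With no treatment effect, about one simulated trial in eight had a baseline difference above 1.5 standard errors. In those trials the Wilcoxon test rejected in 10 to 16% at ρ 0.6, 11 to 17% at 0.7 and 7 to 10% at 0.8. Each figure rests on about 2,500/8 ≈ 310 runs, so its simulation error is about 2 points (√(0.12 × 0.88/310)). Over all randomisations the rate is about 5%.

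**The case against.** A reader might infer that the baseline is thrown away, that the walk result is biased, or that a good deal of power is lost. The document supports none of these.

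- **Baseline is used.** The outcome is change, so each patient's baseline is already subtracted and only the regression-to-the-mean part remains.
- **The test is valid.** Simulated type I error is about 5%. The raised rejection rates under step 5 hold only given an unbalanced draw, and fall as ρ rises.
- **Large gains need other settings.** At α 0.025 and 0.6 SD, with gamma-skewed errors, simulated power rises from about 65% to 70 to 75% for ρ 0.8 to 0.6. The walk test is fixed at 0.05, and 50 m is about 0.88 SD, where the gain almost vanishes.
- **The choice is reasoned.** The plan gives skewness as its reason and prices a 5% loss against a *t*-test into the sample size. Its power does not rely on adjustment, so nothing promised is lost, and the study calls itself a pilot.
- **Estimates are not absent.** Bootstrap intervals are named, and how estimates are reported is often left to an analysis plan that is not shown here.

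All of this stands and limits the point to a modest one. It does not remove it. The 5% allowance is for ranks against a *t*-test, not for omitting the baseline; the intervals are optional and not described as adjusted; and skewness does not explain why one primary outcome is adjusted and the other is not.

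**Conclusion.** The point holds as a free improvement in efficiency and consistency, not as the correction of an error. The unadjusted test leaves about (1 − ρ) of a chance baseline imbalance in the comparison: about 3 to 6.5 m for a one-standard-error imbalance at ρ 0.9 to 0.5, against a standard error of about 13 m. At α = 0.05 and ρ 0.6 to 0.95, adjustment would add about 0 to 3 power points at 50 m and about 1 to 10 at 30 to 35 m.

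These sizes rest on an assumed ρ, equal SDs at the two visits, a two-sided test, an SD of about 57 m back-solved from the stated 93%, and assumed shapes of skew. A reader might also conclude that the walk should simply get the CRQ's ANCOVA. Under the skew that the plan cites, that can cost power, so it does not follow.

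**What to change.** 1. In Efficacy, make the primary 6-minute-walk test a baseline-adjusted rank test on the 12-week change. One choice is Quade's: rank the change and the baseline distance across both arms, regress one on the other, and compare the residuals by arm. State that the change is ranked, not the 12-week value. The test keeps its robustness to skew.
2. Use the same test wherever the plan reuses the Wilcoxon test for walk change (per-protocol analysis and Exploratory aims 1 and 2), with the distance from which that change is measured as covariate. The Wilcoxon comparison of practice hours can stay.
3. Make the optional bootstrap interval definite: a baseline-adjusted between-group difference in metres with a 95% CI. Describe it as an estimate alongside the rank test, because it targets a different quantity and the two can disagree under skew.

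The cost is analysis wording only. Table 1 schedules the walk test at baseline for everyone, randomisation follows baseline testing, and recruitment was still open at publication, so the change could be made before any outcome analysis. Sample size is unaffected.

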#### Secondary aims

The basic analytic approach for secondary efficacy measures will be parallel to the approach for the primary measures, comparing change in outcome from baseline to 12 weeks among the two treatment groups. However, for these secondary measures, we do not anticipate using an adjustment for multiple outcomes. As secondary analyses, we also plan to analyze the change in each of the four CRQ subdomains (dyspnea, fatigue, emotion, mastery) using the same methods.

In addition, we will use linear regression models using primary study outcomes (change in 6-minute walk and CRQ score) as dependent variables and scores on psychosocial assessments and functional tests as potential mediators to examine whether clinical outcome is associated with these psychosocial or physiological parameters. Separate exploratory models will be developed for each primary outcome, providing insight into potential mechanisms of effect.

Qualitative exit interviews will be professionally transcribed from audio recordings and coded using an inductive approach informed by grounded theory methods. We will identify passages in the transcripts that represent common themes or content categories relating to positive, negative, and neutral aspects of patients’ experiences with tai chi, MBB, and education control. Data will be analyzed and presented descriptively according to content categories (as above) [105–108]. We will also examine a per-protocol analysis of our primary outcomes for aim 1, where non-adherers will be excluded (secondary analysis). Non-adherence will be defined as attendance at less than 70% of classes.

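### The sample-size, efficacy and secondary-aims text give conflicting multiplicity rules for the two primary outcomes, and no alpha is stated for the CRQ

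*Protocol article*

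**What the plan says.** Three places in the article's Statistical analysis section bear on this.

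- **Sample size and power.** The study is powered on the "pre-specified primary outcomes of overall CRQ (chronic respiratory questionnaire) score and 6-minute walk-test distance". It claims "approximately 93% power to detect differences between groups of approximately 50 meters change in the 6-minute walk test" and, for the same power, 0.9 points in total CRQ. The figures are said to allow for a "10% dropout rate, and a conservative Bonferroni correction for multiple outcomes", as well as a 5% efficiency loss for the nonparametric walk test.
- **Primary aims, Efficacy.** The CRQ change is analysed by ANCOVA, with no alpha given. The walk change is analysed by a Wilcoxon rank sum test at the 0.05 level, and the article adds that this is done "without the Bonferroni correction, given the pilot feasibility nature of the study".
- **Secondary aims.** The approach parallels that for the primaries, but "However, for these secondary measures, we do not anticipate using an adjustment for multiple outcomes".

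No section says whether an efficacy claim needs one primary outcome or both.

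**The concern.** With two primary outcomes, the alpha per test and the success rule together fix the chance of a false efficacy claim. Here the sizing text assumes a correction, the analysis text removes it for one outcome and is silent on the other, and the contrast drawn for the secondary measures makes sense only if the primaries are adjusted. Someone analysing the trial could defend 0.025 or 0.05 for the CRQ, and could defend claiming efficacy on one outcome or only on both.

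The stake is mainly type I error. If the level and the success rule are settled after the data are seen, the choice can follow the results. A second consequence is that the quoted power refers to a stricter significance level than the one stated for the walk test.

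**Working it through.** **Inputs from the article.** Tai chi 63, education 31; dropout 10%; efficiency loss 5% (walk only); 93% power at 50 m and at 0.9 CRQ points; over 96% at 54 m; 99% at 68 m; dosage aim 82% at 50 m with 21 per group; 0.5 CRQ points called clinically meaningful.

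**Assumptions.** Two-sided tests (sidedness is not stated). Bonferroni over two outcomes means 0.05/2 = 0.025 each (inferred, not printed). No SD is printed, so 93% cannot be reproduced independently and the SD has to be back-solved.

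**1. Walk power.** Effective sizes: 63 × 0.90 × 0.95 = 53.9 and 31 × 0.90 × 0.95 = 26.5. Normal approximation: power = Φ(δ / (SD × √(1/n1 + 1/n2)) − z), with √(1/53.9 + 1/26.5) = 0.2373.

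- At alpha 0.025, z = 2.241. For 93% power the ratio must be 2.241 + 1.476 = 3.717, so SD = 50 / (3.717 × 0.2373) = 56.7 m (55.8 m with the noncentral t).
- The same SD gives 96.2% at 54 m and 99.8% at 68 m, in line with the stated figures.
- At alpha 0.05, z = 1.960: power at 50 m = Φ(3.717 − 1.960) = Φ(1.757) = 96.1%, and 98.0% at 54 m.

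**2. Do the printed powers identify the alpha?** Not by themselves. Solving 93% at 50 m with alpha 0.05 gives an SD of 61.3 m, and then 96.0% at 54 m and 99.7% at 68 m, almost the same pattern. The dosage aim helps. If its 82% is at alpha 0.05 (assumed) with 21 per group, the SD is 56.3 m. That SD gives 93.3% for the primary comparison at 0.025 but 96.2% at 0.05. Taking the 5% efficiency loss off the 21 (19.95 per group) gives an SD of 54.9 m, with 94.5% and 97.0%. So 93% fits the corrected level better, as the Sample size text itself says.

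**3. Familywise error, two-sided, success on either outcome.**

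| Rule | Correlation of the tests | Familywise error |
|---|---|---|
| Both at 0.05 | 0 | 1 − 0.95² = 9.75% |
| Both at 0.05 | 0.3 | 9.5% |
| Both at 0.05 | 0.5 | 9.1% |
| Both at 0.05 | 0.7 | 8.4% |
| Walk 0.05, CRQ 0.025 | 0 | 1 − 0.95 × 0.975 = 7.4% |
| Both at 0.025 | 0 | 1 − 0.975² = 4.9% |

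The correlated values come from the bivariate normal distribution. Counting only false claims in favour of tai chi, two independent tests at 0.05 give 4.9%, against 2.5% with the correction. If both outcomes must succeed, the error cannot exceed 5%.

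**4. What the correction costs on the CRQ.** Sizes after dropout: 56.7 and 27.9, with √(1/56.7 + 1/27.9) = 0.2313. From 93% at 0.9 points and alpha 0.025, SD = 0.9 / (3.717 × 0.2313) = 1.05. At 0.5 points the ratio is 0.5 / (1.047 × 0.2313) = 2.065, so power = Φ(2.065 − 2.241) = 43% at 0.025 and Φ(2.065 − 1.960) = 54% at 0.05. This ignores any gain from baseline adjustment in the ANCOVA.

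**The case against.** The strongest reply is that sizing and testing are separate steps. A trial may be sized at a stricter alpha and tested at 0.05, and the stated power is then a lower bound. The waiver is also disclosed, specified in advance and reasoned: the article calls the trial a pilot and promises preliminary evidence. Unadjusted testing of two named primaries is defensible in that setting.

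Much of this stands. The sizing and efficacy texts can be read together, and the waiver is a legitimate option. What remains is the missing CRQ alpha, the missing success rule, and the Secondary aims contrast, which does not fit a waiver for the primaries. The pilot argument is also weakened, though not refuted, by a primary efficacy aim with a stated power of 93% with the correction already counted.

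Four stronger readings are tempting, and the document does not support them:

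- **That the false-claim rate is nearly 10% as a matter of fact.** This needs the CRQ at 0.05 and success on either outcome, and neither is written. The waiver stands only in the walk sentence, although its reason is study-wide. The hypothesis names quality of life and exercise capacity together, which could be read as requiring both.
- **That the trial lacks power.** The mismatch runs the other way: power at 0.05 is higher than stated.
- **That the 54 m and 68 m figures prove which alpha was used.** They fit both levels.
- **That keeping the correction is almost free.** That holds at 50 m, but not at the 0.5-point CRQ difference the article calls meaningful.

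**Conclusion.** The inconsistency is real and should be resolved before the primary analysis; the article reports recruitment as ongoing. The two-sided familywise error is about 9–10% if both primaries are tested at 0.05 and either can support a claim, and 7.4% (independent tests) if only the walk is uncorrected. There is no inflation if both must succeed. The stated 93% is about 3 points below the power of the 0.05-level walk test at 50 m, on an SD inferred from that same 93%. Because the waiver is openly stated and tied to the pilot nature of the trial, the point is that one coherent rule must be written down. It does not follow that the correction must be restored in every case.

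**What to change.** State one multiplicity rule for both primary outcomes in the Efficacy section, including the success rule, and bring the Sample size and Secondary aims sections into line with it.

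**Preferred.** Replace the parenthesis in the walk sentence with a Holm procedure covering the CRQ and the walk: the smaller p-value is compared with 0.025 and, if that succeeds, the other with 0.05. The Sample size and Secondary aims sections then stand, and the sample size does not change. The cost is one sentence, plus about 3 points of power at 50 m (93% against 96%) and up to about 11 points at a 0.5-point CRQ difference (43% against 54% at a fixed 0.025, assumed SD about 1.05). Holm recovers part of that loss when the other outcome succeeds.

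**If the pilot waiver is kept.** Say that it covers both outcomes at 0.05, restate the power at that alpha, and remove the contrast in the Secondary aims section. Also state that a finding on one outcome alone is preliminary because familywise error is not controlled. This costs a few sentences and no power, but it gives up familywise control.

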##### Safety/feasibility

Study feasibility will be established if we can report that a reasonable proportion of eligible patients are willing to participate (>10%), that we can recruit participants at a reasonable rate (approximately 5 patients per month), and that patients once enrolled will adhere to our study protocol (with at least 70% attendance). Safety will be evaluated through descriptive statistics of AEs and frequencies will be reported per type according to grade and severity per arm. The intervention will be considered safe if there are no serious AEs related to the intervention.

#### Secondary aims

The basic analytic approach for secondary efficacy measures will be parallel to the approach for the primary measures, comparing change in outcome from baseline to 12 weeks among the two treatment groups. However, for these secondary measures, we do not anticipate using an adjustment for multiple outcomes. As secondary analyses, we also plan to analyze the change in each of the four CRQ subdomains (dyspnea, fatigue, emotion, mastery) using the same methods.

In addition, we will use linear regression models using primary study outcomes (change in 6-minute walk and CRQ score) as dependent variables and scores on psychosocial assessments and functional tests as potential mediators to examine whether clinical outcome is associated with these psychosocial or physiological parameters. Separate exploratory models will be developed for each primary outcome, providing insight into potential mechanisms of effect.

Qualitative exit interviews will be professionally transcribed from audio recordings and coded using an inductive approach informed by grounded theory methods. We will identify passages in the transcripts that represent common themes or content categories relating to positive, negative, and neutral aspects of patients’ experiences with tai chi, MBB, and education control. Data will be analyzed and presented descriptively according to content categories (as above) [105–108]. We will also examine a per-protocol analysis of our primary outcomes for aim 1, where non-adherers will be excluded (secondary analysis). Non-adherence will be defined as attendance at less than 70% of classes.

